### Study setting

The setting in which the patients will be recruited and the study visits will be carried out will be the pediatric ophthalmology units of the University Clinical Hospital of Valladolid and the Vithas Medimar International Hospital of Alicante.

On the other hand, the setting in which the necessary equipment will be installed to carry out the active visual therapy sessions with the NEIVATECH system will be a consultation room of the Department of Medicine of the University of Valladolid and the Department of Optics, Pharmacology and Anatomy of the University of Alicante.

All rsfMRI scans that are intended to be performed as part of the study will take place in the Philips Achieva 3.0 T X-Series Scanner of the Laboratory of Instrumental Techniques (LTI) of the University of Valladolid.

### Sampling

Consecutive sampling of all patients attending the pediatric ophthalmology units of the hospital centres planned for recruitment who met the eligibility criteria will be carried out over a period of 12 months (May 2022 to April 2022). The contact details of all patients who consent to participate will be registered in order that they can be contacted to arrange in-office active vision therapy sessions and scheduled visits. Participants will be assigned to the experimental or control group by block randomization using a computer-generated list of random numbers in order to ensure equal treatment allocation. Once randomized, each patient recruited in Valladolid will also be offered the possibility of participating in the rsfMRI study until the proposed number in each group is reached.

Sample size estimation for this study was carried out using the GRANMO online platform (https://www.imim.es/ofertadeserveis/software-public/granmo/), establishing a minimum distance BCVA difference to be detected in both groups before and after the intervention of 0.15 logMAR, a follow-up loss of 10% and a common standard deviation (SD) of 0.195 logMAR. According to this, a sample size of 30 patients per group would be required, considering an alpha error of 0.05 and a statistical power of 80%. This result is consistent with the sample size used in previous studies in this area [36–38].

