## Background

Amblyopia has traditionally been defined as a reduction in the best-corrected visual acuity (BCVA) of one or both eyes in the absence of obvious organic disease [1]. This reduction in BCVA is known to be due to an abnormal binocular experience originating during the critical period of visual system development, which may be caused by a misalignment of the eyes (strabismic amblyopia), a significant difference in the refractive error of the eyes (anisometropic amblyopia) or the presence of an ocular condition that prevents adequate visual stimulation (deprivation amblyopia) [2].

A wide range of large cohort and population-based studies have concluded that the global prevalence of amblyopia averages between 3 and 5%, making it the world’s leading cause of visual impairment in children and young adults [3, 4].

Current treatment of amblyopia emphasizes patching or penalizing the non-amblyopic eye to force the use of the affected eye, and although this is an effective method of improving visual acuity (VA), it has been associated with residual monocular and binocular deficits and a high risk of recurrence and non-compliance [5–7]. Furthermore, it has been argued that this monocular approach rarely results in the establishment of binocular function and is not considered valid in amblyopic patients who are beyond the critical period of visual system development [8, 9]. All these reasons have led to a substantial increase in research in the last decades on new treatment approaches that can satisfy both children and adults, with perceptual learning, video games and binocular treatment methods being the most relevant trends aimed at improving binocular fusion and reducing interocular suppression commonly present in amblyopia [10].

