## Methods

### Hypothesis and aims

We hypothesise that 9 hours of therapy with the NEIVATECH system, which combines dichoptic training with perceptual learning tasks and gamified elements in an immersive virtual reality (VR) environment, will provide greater improvements in visual function in children with anisometropic amblyopia than conventional patching.

To test our hypothesis, we intend to conduct a small-scale RCT in which 60 anisometropic amblyopic children aged 5-17 years with no history of treatment for amblyopia other than refractive correction alone will be randomly assigned to receive 18 half-hour active vision therapy sessions with the NEIVATECH system over a period of 3 months (group A) or 2 hours of daily patching at home for the same period of time (group B).

The primary outcome measure to be considered will be changes in distance BCVA before and after therapy. Secondary outcome measures will include near BCVA, CSF, binocular vision, stereopsis, fusional vergence, near convergence point and accommodative facility. Other valuable outcome measures to consider after the intervention will be satisfaction, adherence, acceptance and safety of the therapy. In addition, resting-state fMRI (rsfMRI) will also be performed on a subgroup of 5 patients from each group at the pre- and post-intervention visit to provide a rational explanation for the visual improvements obtained with the NEIVATECH system, if any.

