### Study design

This is a multicentre, open-label, small-scale RCT involving two tertiary hospital centres with an on-site pediatric ophthalmology unit in their facilities. The protocol for this study was designed according to the SPIRIT (Standard Protocol Elements: Recommendations for Interventional Trials) 2013 Statement (Supplementary file 1). Patients will be offered to participate in the study once they have been found to meet all inclusion criteria without fulfilling any exclusion criteria (Table 1).

**Table 1 Tab1:** Eligibility criteria for participation in the NEIVATECH RCT

Inclusion criteria	
- Children aged between 5 and 17 years. - Willingness to perform the assigned therapy and to carry out the established visits. - No history of previous treatment for amblyopia other than optimal refractive correction for at least 2 months prior to inclusion in the study. - BCVA in the amblyopic eye of ≤0.1 logMAR with at least 1 logMAR line difference between the two eyes of the same patient. - Presence of anisometropia defined as a difference in spherical equivalent between the two eyes of ≥1.5 dioptres.	
Exclusion criteria	
- Active eye disease. - Previous ocular surgery. - BCVA in the amblyopic eye of ≥0.70 logMAR. - Presence of strabismic or deprivation amblyopia. - Presence of microtropia or intermittent strabismus. - Presence of irregular cornea due to astigmatism or ectatic corneal disease. - Presence of psychiatric or neurological disorders or cognitive impairment.	

Prior to participation, trained research staff will obtain written informed consent from the patient or the patient’s parents or legal guardians depending on whether the patient is older or younger than 16 years of age. For the rsfMRI study, patients will have to meet specific eligibility criteria and sign a separate informed consent form to undergo testing (Table 2).

**Table 2 Tab2:** Eligibility criteria for participation in the rsfMRI study

Inclusion criteria	
- Inclusion in the NEIVATECH RCT. - Written informed consent for rsfMRI.	
Exclusion criteria	
- Claustrophobia. - Pregnancy or breastfeeding. - Presence of a pacemaker or other cardiac device. - Presence of an external or implantable insulin pump. - Presence of metallic implants or intracorporeal foreign bodies.	

Patients may leave the study once they have completed all visits as outlined in the protocol or whenever they wish by contacting the principal investigator and signing a waiver form.

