### Study overview

Participation in this RCT will essentially involve five visits (screening, pre-intervention visit, one-month visit, two-month visit and post-intervention visit), in addition to the visits that patients assigned to group A will have to make to carry out the active vision therapy sessions with the NEIVATECH system. These sessions will be 18 in total, will have an average duration of half an hour and will be distributed as follows: five sessions in the first week (Monday to Friday), three sessions in the second week (Monday, Wednesday and Friday) and a maintenance session in the following weeks (on Wednesdays). This is because it has been shown that most of the improvement obtained with visual training in amblyopia occurs during the first weeks of treatment [39–41]. Thus, patients assigned to group A will have to perform 10 sessions of active vision therapy with the NEIVATECH system during the first month of treatment, 4 during the second month and 4 during the third month. On the other hand, patients assigned to group B will have to comply with 2 hours of daily patching during the 3 months of the study.

In addition, a subgroup of 5 patients from group A and 5 patients from group B will have to make two additional visits to the LTI of the University of Valladolid before and after the intervention for a rsfMRI scan (Fig. 3).

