### Data analyses plan

A professional biostatistician has been consulted to design the data analysis plan for the study, in which descriptive analysis of all data will be provided, including means and SDs or medians for continuous variables and proportions for categorical variables.

Variables will be analyzed to assess distribution/normality (Kurtosis and Skewness) and by histogram analysis to establish whether they will be analyzed with parametric or non-parametric tests. On the one hand, parametric data will be analyzed using the unpaired T-test, Analysis of Variance (ANOVA) for comparison between groups and multiple linear regression to predict values according to the variables of interest. On the other hand, non-parametric data will be analyzed using the Mann-Whitney U test or the Chi-squared test, the Kruskal-Wallis H test and other non-parametric methods.

For the purposes of the rsfMRI study, analyses of grey matter, white matter diffusion and functional connectivity will be performed. To quantify the variation between the metrics obtained in the two acquisitions (pre-intervention and post-intervention), a coefficient of variation of (Mt_0_ − Mt_1_ / Mt_0_) × 100 will be used, where M will be the metric considered, t_0_ will correspond to the first acquisition (pre-intervention visit) and t_1_ will correspond to the second acquisition (post-intervention visit).

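### The stated randomisation and primary group comparison name no age or centre factor, so at 60 children aged 5 to 17 some precision is lost and chance imbalance goes uncorrected

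*Protocol article*

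**What the plan says.** All references are to the protocol article.

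- **Allocation (Sampling).** "Participants will be assigned to the experimental or control group by block randomization using a computer-generated list of random numbers", and the reason given is "in order to ensure equal treatment allocation". No stratification factor is named.
- **Population (Hypothesis and aims; Study design, Table 1).** The trial plans "60 anisometropic amblyopic children aged 5-17 years"; the inclusion criterion reads "Children aged between 5 and 17 years". It is a multicentre trial "involving two tertiary hospital centres".
- **Comparator (Study overview).** "patients assigned to group B will have to comply with 2 hours of daily patching during the 3 months of the study", with no distinction by age.
- **Age and the comparator (Background).** The opening section reports, as something that has been argued in cited work, that the monocular approach "is not considered valid in amblyopic patients who are beyond the critical period of visual system development". It gives no age at which that period ends. The Video games subsection then cites a study of 385 previously untreated children aged 5 to 12 and 13 to 16, in which binocular games did not do as well as 2 hours of occlusion.
- **Analysis (Data analyses plan).** "parametric data will be analyzed using the unpaired T-test, Analysis of Variance (ANOVA) for comparison between groups"; the Mann-Whitney test is named for data judged non-parametric. Multiple linear regression is also listed, but as a way to predict values from variables that are not identified. It is not tied to the primary comparison of distance BCVA.

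**The concern.** Blocking for equal allocation balances the number of children per arm. It does not balance who they are. The article's own background makes age a plausible influence on the response to patching. Centre is a plausible influence too, because under Study setting each city delivers the NEIVATECH sessions in its own university department. With 30 children per arm, the age mix can differ noticeably by chance. An unpaired t-test or Mann-Whitney test takes no account of such a difference.

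Two things are at stake. The first is precision: the trial is sized at about 80% power, and variation that a covariate known at screening could explain is left in the error term. The second is interpretation: if the arms turn out to differ in age, the stated comparison gives the reader no way to tell how much of the observed difference reflects that.

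**Working it through.** **1. The plan's own figure.** Inputs from Sampling: difference 0.15 logMAR, SD 0.195, alpha 0.05 (two-sided reproduces the result), power 80%, loss 10%.

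- n per arm = 2 × [0.195 × (1.96 + 0.84) / 0.15]² = 26.5, rounded up to 27.
- 27 / 0.90 = 30 per arm. The stated 30 is reproduced and does not depend on stratification.

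**2. Chance difference in mean age.** Assumption (not in the article): ages uniform over 5 to 17.

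- SD of age = 12 / √12 = 3.46 years.
- 95% range of the difference in means, 30 per arm = 1.96 × 3.46 × √(2/30) = ±1.75 years.

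**3. Effect on the estimate.** Assumption (not in the article): the gain in BCVA changes by 0.02 logMAR per year of age in both arms.

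- 1.75 × 0.02 = ±0.035 logMAR; 0.035 / 0.15 = 23% of the target difference.
- If the slope exists in the patching arm only, that arm's mean age departs from the whole sample's mean by half as much, so the shift is about ±0.018 logMAR.

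**4. A second route with other assumptions.** Suppose older children make up 20% to 50% of the 60 and differ from younger ones by 0.05 to 0.15 logMAR in expected change (both assumed).

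- Hypergeometric probability that the arms differ by at least 6 older children (6/30 = 20 percentage points): 0.10 to 0.20.
- Shift from a 20-point imbalance: 0.20 × 0.05 = 0.01 to 0.20 × 0.15 = 0.03 logMAR, or 7% to 20% of the target.

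**5. What adjustment buys.** If 0.195 already contains the variation due to age:

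- Unadjusted 95% half-width at 30 per arm = 1.96 × 0.195 × √(2/30) = 0.099 logMAR.
- With the age part of step 3 removed: √(0.099² − 0.035²) = 0.092 logMAR, about 7% narrower.
- In power terms, with residual SD = 0.195 × √(1 − r²) and 27 evaluable per arm, where r is the assumed correlation of age with outcome:

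| r (assumed) | Residual SD | Power |
|---|---|---|
| 0 | 0.195 | 81% |
| 0.2 | 0.191 | 82% |
| 0.3 | 0.186 | 84% |
| 0.5 | 0.169 | 90% |

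The slope in step 3 corresponds to r = 0.02 × 3.46 / 0.195 = 0.36. Any gain from baseline BCVA would be additional and is not quantified here.

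**6. How much a by-age estimate could show.** With 12 and 18 children per arm in two age bands (assumed, 40% in the older band):

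- SE of the interaction = 0.195 × √(2/12 + 2/18) = 0.103 logMAR.
- Interaction detectable with 80% power = 2.80 × 0.103 = 0.29 logMAR, nearly twice the target difference.

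**The case against.** The strongest reply is that the article is silent and has not decided against these factors. It never says the block list is unstratified, and a condensed article commonly leaves stratification factors and covariates to the full protocol or analysis plan. Regression is listed, so adjustment is not ruled out. This stands as far as randomisation goes: no more can be said than that no factor is named. It does not dispose of the analysis point. The article does name the tests for the group comparison, those tests carry no covariates, and the regression is described as prediction and not as the comparison.

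A second reply is that chance imbalance is not bias. It can favour either arm, and it is already reflected in the standard error and the type I error rate. This is correct, and it limits the point to precision and interpretability. The ±0.035 logMAR is a 95% limit, not an expected shift.

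Two stronger readings are tempting. A reader might infer that the article itself regards patching as invalid for the older children it enrols, so that an apparent advantage for NEIVATECH could come from ages where the comparator does not work. The text does not support this: the Background reports an argument, gives no age, and does not place any of the 5 to 17 range beyond the critical period. The same Background cites patching doing better than binocular games in children up to 16. A reader might also want the conclusion confined to the ages in which a difference is shown. Step 6 shows why that fails: the conclusion would rest on underpowered subgroups.

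**Conclusion.** The point holds in a limited form. The unadjusted comparison described in the article is valid, and the sample size reproduces. What can be improved is that a plausible prognostic factor (age) and a design feature (centre) are absent from both the stated randomisation and the stated primary comparison.

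The size is modest. The limit of ±0.035 logMAR, in either direction, rests on uniform ages and a slope of 0.02 logMAR per year; the second route gives 0.01 to 0.03 for a 20-point imbalance. The corresponding gain from adjustment is about 7% in interval width, or one to nine percentage points of power for r between 0.2 and 0.5. None of the age inputs is in the article, so these figures are illustrations. The case for change rests mainly on its very low cost.

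**What to change.** For the primary outcome, replace the unpaired t-test with a linear model (ANCOVA) of 3-month distance BCVA on arm, with baseline BCVA, age (continuous) and centre as covariates, stated before any outcome data are seen.

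If enrolment has not begun, also stratify the block list by centre and, if practical, by two age bands. Four strata average 60 / 4 = 15 children each, which is workable. The article gives no age for the critical period, so any cut point is an administrative choice and should be described as one. If enrolment has begun, the adjusted model alone is sufficient. If a fuller document already names these factors, stating them is enough.

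Report the treatment-by-age estimate with its 95% CI as descriptive only, and do not let it decide the trial's conclusion.

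Cost: slightly more list administration, and three degrees of freedom in the model (with 54 evaluable children, 54 − 5 = 49 residual degrees of freedom against 54 − 2 = 52 for the t-test). Age, centre and baseline BCVA are all collected before treatment starts. N stays at 30 per arm.

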### Intervention

The NEIVATECH VR-based system has been conceived as a Serious Game designed to provide dichoptic training to amblyopic children by discriminating the direction of Gabor patches presented with different contrast to each eye as a perceptual learning task. Patients have to identify the same Gabor patch as the one presented at the start of the game, all in different VR environments where immersion will be achieved using the HTC Vive Pro Head Mounted Display (HMD) and interaction will be achieved using the VR Developer Mount system. The NEIVATECH system is also equipped with software to configure the characteristics of the visual stimuli presented to users according to their vision (Fig. 1) and to record the results obtained by the user in each session, facilitating the analysis and evaluation of individual progress over time.

**Fig. 1 Fig1:**
[figure not shown]
Menu to configure the characteristics of the visual stimuli to be presented to the user in the VR environment

### Patient and public involvement

A total of 22 children (14 boys, 8 girls, mean age: 10.36 ± 1.76 years) participated in the design of the VR scenarios that make up the Serious Game by providing feedback on the initially designed scenarios and suggestions on the incorporation of new elements to make them more attractive to the target population. For this purpose, a visual analogue scale created by the research team was used to record patients’ opinions and requests. Figure 2 shows an example of a scenario (Space) with the discrimination task to be performed.

**Fig. 2 Fig2:**
[figure not shown]
Example of a VR scenario incorporated into the NEIVATECH system

### Study overview

Participation in this RCT will essentially involve five visits (screening, pre-intervention visit, one-month visit, two-month visit and post-intervention visit), in addition to the visits that patients assigned to group A will have to make to carry out the active vision therapy sessions with the NEIVATECH system. These sessions will be 18 in total, will have an average duration of half an hour and will be distributed as follows: five sessions in the first week (Monday to Friday), three sessions in the second week (Monday, Wednesday and Friday) and a maintenance session in the following weeks (on Wednesdays). This is because it has been shown that most of the improvement obtained with visual training in amblyopia occurs during the first weeks of treatment [39–41]. Thus, patients assigned to group A will have to perform 10 sessions of active vision therapy with the NEIVATECH system during the first month of treatment, 4 during the second month and 4 during the third month. On the other hand, patients assigned to group B will have to comply with 2 hours of daily patching during the 3 months of the study.

In addition, a subgroup of 5 patients from group A and 5 patients from group B will have to make two additional visits to the LTI of the University of Valladolid before and after the intervention for a rsfMRI scan (Fig. 3).

**Fig. 3 Fig3:**
[figure not shown]
Diagram of the NEIVATECH RCT protocol

### Pre-intervention (day 0)

Once the patient has been found to meet the eligibility criteria required for participation and the informed consent form has been signed, he/she will be seen in consultation prior to receiving the assigned intervention for a comprehensive eye examination including cycloplegic autorefraction and assessment of near and distance BCVA (monocular and binocular, logMAR scale, using the ETDRS chart), CSF (monocular, using the CSV-1000 test for spatial frequencies of 3, 6, 12 and 18 cycles per degree), binocular vision (using the Worth’s four-dot test), stereopsis (using the TNO stereoscopic test), fusional vergence (break and recovery), accommodative facility (measured as the number of changes made to achieve optimal focusing using a spherical flap of ±2 dioptres when the patient looks at a near optotype: VA 0.2 logMAR) and near convergence point (measured as the closest distance in centimetres in reference to the patient’s nasal root at which he/she is able to maintain single vision).

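### Accommodative facility uses one fixed 0.2 logMAR near target; if the amblyopic eye is tested alone, eyes with worse near acuity have counts limited by acuity rather than accommodation

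*Protocol article*

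**What the plan says.** Under Hypothesis and aims, accommodative facility is a secondary outcome in its own right, listed separately from near acuity: "Secondary outcome measures will include near BCVA, CSF, binocular vision, stereopsis, fusional vergence, near convergence point and accommodative facility".

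Under Pre-intervention (day 0), the measure is "accommodative facility (measured as the number of changes made to achieve optimal focusing", and it is taken "using a spherical flap of ±2 dioptres when the patient looks at a near optotype: VA 0.2 logMAR". One target size therefore serves every child. The later visit sections repeat the visual measures at one, two and three months.

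The same paragraph gives the viewing condition for acuity, "near and distance BCVA (monocular and binocular, logMAR scale, using the ETDRS chart", and for contrast sensitivity, "CSF (monocular, using the CSV-1000 test". It gives none for facility.

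Two lines of Table 1 (Study design) bear on which eyes enter. The inclusion line reads "BCVA in the amblyopic eye of ≤0.1 logMAR with at least 1 logMAR line difference between the two eyes of the same patient". The exclusion line reads "BCVA in the amblyopic eye of ≥0.70 logMAR".

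**The concern.** Facility is meant to show how readily the eye changes focus. The count depends on the child judging that the target has become clear. An eye whose near acuity is worse than the target size cannot make that judgement, however well it accommodates.

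If such eyes are enrolled and tested alone, their baseline count reflects acuity. When treatment brings acuity past 0.2 logMAR, the count can rise although accommodation is unchanged. Acuity is what the trial expects to differ between arms, so an acuity difference could partly reappear as a facility difference and be read as a separate benefit.

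If both eyes are open, the fellow eye, at least one line better, may read the target. The Background describes interocular suppression as common in amblyopia. A child who suppresses could then be scored on the fellow eye, and the count would say little about the eye or the binocular system under treatment.

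**Working it through.** **The plan's own figure.** The only calculated figure is the sample size, "establishing a minimum distance BCVA difference to be detected in both groups before and after the intervention of 0.15 logMAR", with SD 0.195, alpha 0.05, power 80% and 10% loss.

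- n per group = 2 × (1.960 + 0.842)² × 0.195² / 0.15² ≈ 26.5, rounded up to 27 (two-sided).
- 27 / (1 − 0.10) = 30 per group.

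This reproduces the stated 30. It concerns distance BCVA, and nothing below alters it.

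**Which eyes enter.** Lower logMAR is better acuity.

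- As printed, the inclusion line admits amblyopic eyes at 0.1 or better. Taking near acuity as similar to distance acuity, 0% would fail a 0.2 target.
- The exclusion at 0.70 or worse would then remove nobody, because no eye at 0.1 or better could reach it. It has a function only if eyes worse than 0.1 are meant to enter.
- A planned difference of 0.15 logMAR with SD 0.195 is also hard to square with all amblyopic eyes starting at 0.1 or better.

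The two lines must be reconciled. The rest assumes an intended span of 0.1 to just under 0.70 logMAR, with near acuity similar to distance acuity. The document gives no baseline distribution, so the shapes below are assumptions.

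**Share worse than 0.2 at baseline, amblyopic eye tested alone.**

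- Uniform on 0.10 to 0.70: (0.70 − 0.20) / (0.70 − 0.10) = 0.50 / 0.60 = 83%.
- Normal, truncated to the same span:

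| Location (logMAR) | SD 0.10 | SD 0.15 | SD 0.195 |
|---|---|---|---|
| 0.15 | 44.6% | 58.6% | 66.2% |
| 0.20 | 59.4% | 66.9% | 71.6% |
| 0.30 | 86.1% | 82.2% | 81.7% |
| 0.40 | 97.9% | 92.8% | 89.7% |
| 0.50 | 99.9% | 97.9% | 94.9% |

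The range is about 45% to nearly 100%.

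**Share crossing 0.2 if every eye gained 0.15 logMAR.** These are the eyes that start between 0.20 and 0.35.

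- Uniform: 0.15 / 0.60 = 25% cross; (0.70 − 0.35) / 0.60 = 58% stay worse than 0.2; (0.20 − 0.10) / 0.60 = 17% were never limited by the target.
- Truncated normals: 6.7% (location 0.50, SD 0.10) to 54.5% (location 0.30, SD 0.10) cross.

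For example, an eye moving from 0.30 to 0.15 passes from unable to able to resolve the target with no change in accommodation.

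**Both eyes open.** The fellow eye can supply the response, so there need be no floor. The described procedure has no check that the amblyopic eye is contributing. The document offers nothing from which to estimate how often this would matter.

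**The case against.** A reader might infer that most eligible amblyopic eyes cannot see the target, that they score zero at baseline, and that the endpoint then rises with acuity alone. The documents do not support that, for these reasons.

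- **Eligibility.** On the printed inclusion limit no eye fails the target. Any affected share needs the other reading of Table 1.
- **Viewing eye.** It is not stated. Facility is listed alongside binocular tests, so a binocular test is a natural reading, and then there need be no floor. The full protocol may settle this, so its absence from the article is not itself a fault.
- **Zero score.** No rule is given for a child who cannot resolve the target. A zero is an inference.
- **The 83%.** It is a share of a numerical interval under an assumed uniform shape, with distance acuity standing in for near. One mild-severity case gives 45%, so even a majority is not certain.
- **Acuity alone.** Under the uniform assumption a 0.15 gain takes only 25% of eyes across the threshold. The 0.15 also works as a between-arm difference in the sample size, not as a gain promised for each child.
- **Stakes.** This is one of seven secondary outcomes, and nothing says that a facility gain would be reported as independent of acuity.
- **Remedy.** A target fixed relative to baseline acuity still becomes easier to see as acuity improves.

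All of these stand as limits on the size and wording of the point. They do not remove it. The single target size is a stated choice, not an omitted detail, and it is poorly matched to the range of acuity that the exclusion limit implies. Worth's four-dot test at the same visit records binocular status, but does not show which eye responded during the facility test.

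**Conclusion.** The point holds conditionally. If amblyopic eyes up to just under 0.70 logMAR are enrolled and tested alone, those with near acuity worse than 0.2 have facility counts limited by acuity, and these counts can rise as acuity crosses 0.2 without any accommodative change. The share affected is unknown: about 83% on a uniform assumption, about 45% to nearly 100% on the others tried, all taking near acuity as similar to distance acuity. If both eyes are open, the problem is instead that a suppressing child may be scored on the fellow eye, and its frequency cannot be estimated.

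The consequence is confined to the interpretation of one secondary outcome. The firmest textual point is that the two acuity limits in Table 1 conflict.

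**What to change.** 1. Reconcile the inclusion and exclusion limits for amblyopic-eye BCVA in Table 1.
2. Specify that facility is measured monocularly on the amblyopic eye, with a near target a fixed step (for example two lines) larger than that eye's baseline near BCVA. Keep that size at all visits and record it.
3. If a binocular count is also taken, include a suppression check and state how a suppressed response is scored.
4. Interpret any between-arm difference in facility alongside the change in near BCVA, because scaling the target reduces the dependence on acuity without removing it.

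The cost is small: procedural wording and a near card with several line sizes. Near BCVA is already measured at the baseline visit, so the target size can be set then. The downside is that target size differs between children. The change should precede baseline testing, because a baseline count limited by the target cannot be recovered later.
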